#### Secondary outcomes

Secondary analyses will be evaluated between groups based on data type. Outcome measures that are continuous will be evaluated using the *t*-test, Wilcoxon sign rank test (where appropriate) or through linear regression analysis if important variables are not evenly distributed between groups. Binary secondary outcome measures (for example, hypercalcemia, hypercalciuria) will be compared between the two treatment groups using Fisher’s exact or Chi-square. For the analysis of outcomes measures that represent time to event (for example, restoration of 1,25OH_2_D levels to normal range, time to extubation, and PICU length of stay/discharge), we will apply the log rank test. If randomization does not lead to equal distribution of important variables (for example, weight) the analysis will be expanded to multiple regression modeling (for example, logistic, linear, Cox proportional hazard).

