### Study design

The trial is a single center, double blind, parallel, randomized, controlled dose evaluation trial comparing the efficacy and safety of two vitamin D dosing regimens in the prevention of postoperative vitamin D deficiency in children undergoing surgery for CHD.

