### Randomization, blinding and stratification procedures

We will use a computer-generated randomization sequence. Only the CHEO pharmacy will have access to the randomization sequence and will be responsible for participant randomization and allocation. Only the pharmacist will know the identity of the study drug administered to specific patients. Given the expected recruitment (two to three per month) and potential impact of season on 25OHD, randomization will be performed in permuted blocks (four within each stratum). We will blind patients, families, investigators, hospital staff, and research personnel to treatment arm. Blinding was considered necessary to avoid (i) families altering the outpatient dose and (ii) a number of secondary outcome measures are that are potentially subjective (echocardiography, timing of extubation, need for fluids or catecholamine infusion). Within each age group, the two interventions will be indistinguishable (vial, volume, color, taste, consistency and smell).

Participants will be stratified into whether or not they are expected to receive at least 8 weeks of study drug prior to surgery. This stratification should guarantee that an equal number of CHD patients who will not receive 8 weeks of oral dosing end up in both the high and low dose arms. We will further stratify by age (under or over 1 year of age).

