#### Postoperative biological samples and other study measurements

**Blood** - All study participants will have 2 mL of blood collected following separation from cardiopulmonary bypass (at admission to PICU). Table 4 shows the biomarkers to be measured. Further, study participants will have 2 mL of blood collected on postoperative days 1, 3, 5 and 10 in the PICU. Samples will be collected from arterial or central venous catheters at the time of clinically indicated blood work. If these catheters have been removed, blood will be collected at the time of clinically indicated venipuncture. If patients are discharged to the ward before the day 10 research sample is collected, a discharge sample will be collected at the time of discharge and no further research blood will be gathered. To limit the volume of research blood collected, neonates will only have 1 mL of blood collected postoperatively on days 3, 5, and 10.

**Urine** - All study participants will have urine collected from the urinary catheter on the first postoperative day. Calcium and creatinine concentrations will be determined.

**Echocardiography** - A comprehensive exam will be performed immediately postoperatively (standard of care) and on the first postoperative day by a trained technician or pediatric cardiologist. Between-group comparisons will evaluate for differences in left-ventricular in (LV) end-diastolic diameter, LV end-systolic diameter, and LV ejection fraction [34].

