#### Descriptive statistics

Treatment groups will be described and compared using (i) means with standard deviations or medians with inter-quartile range values for continuous variables or (ii) frequencies with percentages for categorical variables. Statistically significant differences will be determined using Chi-square and Fisher’s exact tests for categorical variables, and t-tests or nonparametric tests (for example, Wilcoxon) for continuous variables, as appropriate.

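### The protocol names the Wilcoxon signed-rank test, a paired or one-sample test, for comparing continuous secondary outcomes between two independent arms; it should name the rank-sum test.

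*Protocol article*

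**What the plan says.** The Secondary outcomes section of the protocol article sets its purpose in its first sentence: "Secondary analyses will be evaluated between groups based on data type". It then assigns tests by data type. For continuous outcomes the tests are the t-test, "Wilcoxon sign rank test (where appropriate) or through linear regression analysis if important variables are not evenly distributed between groups". Binary outcomes go to Fisher's exact or chi-square, and time-to-event outcomes go to the log-rank test.

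The Study design section describes the arms as parallel: "The trial is a single center, double blind, parallel, randomized, controlled dose evaluation trial comparing the efficacy and safety of two vitamin D dosing regimens". Under Randomization, blinding and stratification procedures, "randomization will be performed in permuted blocks (four within each stratum"), with strata formed by expected duration of study drug (at least 8 weeks or not) and by age (under or over 1 year).

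The only other nonparametric test for continuous data appears under Descriptive statistics, for comparing the treatment groups: "t-tests or nonparametric tests (for example, Wilcoxon) for continuous variables, as appropriate". It does not say which Wilcoxon test is meant.

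**The concern.** The signed-rank test ranks the absolute values of within-pair differences, or of one sample's deviations from a fixed value. It is the nonparametric counterpart of the paired t-test. For two independent groups, the counterpart of the two-sample t-test is the Wilcoxon rank-sum (Mann-Whitney) test. The protocol places the signed-rank test in the rank-sum test's position, as the alternative to the t-test in a between-group comparison.

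The outcomes that could reach this test include cathelicidin, maximum inotrope score and 48-hour fluid balance (Organ function and ICU outcome measures), and the echocardiographic measures, for which the protocol says "Between-group comparisons will evaluate for differences in left-ventricular in (LV) end-diastolic diameter, LV end-systolic diameter, and LV ejection fraction". The protocol gives no distributions for these. With about 28 children per arm, some could plausibly be skewed enough for the nonparametric option to be chosen. An analyst would then have to follow a rule that cannot be applied without inventing pairs, or depart from the published plan without a record of why.

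**Working it through.** **Plan's own figure.** The disputed sentence states no number. The figure to protect is the sample size: 28 per arm for 80 % power, 40 % against 80 % above 50 nmol/L, two-sided Fisher's exact test at 0.05, and about 62 in total with 10 % drop-out (Sample size justification).

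- The continuity-corrected two-proportion formula gives 28 per arm.
- Exact enumeration of Fisher's test gives power 0.823 at 28 per arm.
- For drop-out, 56 × 1.1 = 61.6, rounded up to 62; 56 / 0.9 = 62.2, rounded up to 63. Both agree with an approximate 62.

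The sample size therefore reproduces. It rests on Fisher's test alone, so the name of the Wilcoxon test does not enter it.

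**Does the named test match the design?**

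| Element | What the protocol gives | What the signed-rank test needs |
|---|---|---|
| Units | Different children in two parallel arms | Pairs, or one sample |
| Allocation | Permuted blocks of four within strata | A defined partner for each child |
| Comparison | Between groups | Within pairs |

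A block of four holds two children per arm but does not say which belongs with which, and the protocol describes no matched analysis.

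**Are equal arm sizes assured?** No. Two stratification factors with two levels each give 2 × 2 = 4 strata. With 1:1 allocation, an unfinished block of four can leave an imbalance of up to 2, so the total imbalance can reach 4 × 2 = 8 before any drop-out. With 28 children in one arm and 27 in the other, the paired calculation stopped with an error. At least one child would have to be discarded, and the protocol gives no rule for choosing which.

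**What happens with equal arms?** The settings below are assumptions, not protocol figures: independent lognormal arms with log-SD 1, and 4,000 simulated trials per setting.

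| n per arm | Log-shift | Signed-rank, arbitrary pairing: proportion with p < 0.05 | Rank-sum: proportion with p < 0.05 |
|---|---|---|---|
| 28 | 0 | 0.0495 | 0.048 |
| 28 | 0.8 | 0.745 | 0.808 |
| 31 | 0 | 0.0445 | 0.0435 |
| 31 | 0.8 | 0.798 | 0.856 |

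The false-positive rate holds near 0.05 for both tests. The power loss is 0.808 − 0.745 = 0.063 at 28 per arm and 0.856 − 0.798 = 0.058 at 31. It depends on the assumed shape: a repeat with normal data showed a much smaller gap.

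**Dependence on the pairing.** One simulated data set (28 per arm, log-shift 0.6) was held fixed and only the pairing was shuffled, 2,000 times. The signed-rank p-value ran from 0.0005 to 0.17, with median 0.022 and central 95 % of values from 0.003 to 0.081. The rank-sum p-value for the same data is 0.038 whatever the record order.

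**The case against.** **It is a slip of the pen.** The sentence concerns comparison between groups, the test stands beside the t-test, and Descriptive statistics compares the same groups with an unspecified Wilcoxon test. No passage tells anyone to pair unrelated children, and a competent analyst would read rank sum. This is probably right, and it limits the seriousness. It does not remove the error, because the only fully named nonparametric test in the document is the wrong one.

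**The qualifier about appropriateness, and the repeated samples.** Blood is taken from the same child before and after surgery, and Vitamin D axis function speaks of changes in the active hormone. A signed-rank test could suit a within-child change in one arm. However, the section describes no such analysis. It is about differences between groups, and a change score compared between arms still needs a two-sample test.

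**The consequences are limited.** This stands. A reader might infer that the p-values would be invalid or the false-positive rate inflated; the simulation does not support that, since random pairing kept the error rate near 0.05. A reader might also note that 28 children per arm can be paired in 28! ways and infer as many p-values. Without ties, the signed-rank statistic takes only the integers 0 to 28 × 29 / 2 = 406. That is 407 values, symmetric about 203, and so at most 204 distinct two-sided p-values. Nor would every skewed secondary outcome be affected: times to extubation and PICU discharge go to the log-rank test, and continuous outcomes may go to linear regression if important variables are uneven.

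**Conclusion.** The point holds as an error in a stated analysis rule: the named test does not fit the comparison it is assigned to, and nothing in the document corrects it. The harm if followed literally is a result that depends on an arbitrary pairing, loss of children when arm sizes differ, and some loss of efficiency (about 0.75 against 0.81 under the assumed lognormal data). The size of that loss, and whether any outcome is skewed enough to reach the test, rest on assumptions that the protocol neither confirms nor excludes.

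The reach is limited to continuous secondary outcomes sent to the nonparametric option. The documents do not support reading the sentence as a deliberate paired analysis, or as a threat to the trial's main conclusion.

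**What to change.** In Secondary outcomes, replace the signed-rank test with the Wilcoxon rank-sum (Mann-Whitney) test. Use the same full name in Descriptive statistics, where only Wilcoxon appears, so that the two sections agree. If a within-child analysis is intended anywhere, state it separately and keep the signed-rank test for that.

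The cost is a change of test name in two places. No sample size, power figure, data collection or primary analysis changes. Stratifying the rank test by the randomization factors, or reporting a Hodges-Lehmann difference with its confidence interval, is optional and not needed to correct the error.

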#### Subgroup analysis

The well-known pharmacology of enteral vitamin D dosing shows that up to 2 months of regular daily intake is required to build body stores and achieve steady state blood levels of vitamin D. Consequently, neonates or other infants enrolled into the study who receive surgery within two months of birth or CHD diagnosis will be analyzed separately. Within this subgroup analysis, the primary objective remains reporting of the proportions (in the usual care and high dose groups) that are vitamin D deficient postoperatively. However, given that these participants will receive study drug for a very short period, we anticipate that the proportion with 25OHD levels above 50 nmol/L will remain low in the high dose group. Our program goal at this stage is to identify a dosing regimen that prevents postoperative vitamin D deficiency in 75 % of CHD patients. Given this goal, and an estimated prevalence of 25 % we would need 12 neonates (or children who receive <2 months) to generate a confidence interval that excludes 75 %.

*Feasibility—*Most neonates with CHD who require cardiac surgery within the first few weeks of life have serious cardiac lesions that can limit enteral nutrition and medication delivery. Anticipating that most of these patients will not significantly elevate 25OHD levels with daily enteral intake at IOM high dose, this study will provide important information on the willingness of health care providers to provide enteral study drug. This information will allow us to consider alternative dosing regimens for future studies based on single or divided doses representing one or more months worth of daily dosing (for example, 5 to 10,000 IU/kg). Only those children completing the entire study protocol will be included in analyses.

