#### Prior to initiation of study drug

**Urine** - After consent is obtained and the study participant is waiting for the pharmacy to prepare the study drug, we will gather a urine sample for determination of calcium:creatinine ratios. Where developmentally appropriate, the participants will be asked to provide urine into a container. Urine bags will be placed on younger children. If the child is unable to provide a urine sample during the time it takes to fill the study drug prescription, the participant will be provided with a container or urine bag and asked to provide an outpatient urine sample.

**Blood** - Neonates and other study participants requiring surgery within 2 months of diagnosis and enrollment will have 0.5 to 1 mL of blood collected prior to (or within 2 days) of starting the study supplement for determination of 25OHD. Where possible, unused or discarded blood will be obtained from the laboratory [68]. If unused blood is not available, research blood will be collected at the time of clinically indicated blood work, or not at all. These patients will not have blood collected for research purposes again until they are taken to the operating room.

* Note - We will request initiation samples but children will still be enrolled if these samples cannot be collected or the families do not want these procedures.

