### Statistical analysis

#### Sample size justification

Based on our observational studies and findings from recent dose evaluation studies on healthy children, we estimate that no more than 40 % of the usual care arm will have postoperative 25OHD levels above 50 nmol/L. Based on the 25OHD levels achieved with 1600 IU/day in recent studies on approximate IOM high dose in healthy children, we anticipate that 80 % of the high dose arm will have postoperative levels above 50 nmol/L. Therefore group sample sizes of 28 in both treatment arms will be required to achieve 80 % power to detect an absolute difference between the group proportions of 0.40. The test statistic used is the two-sided Fisher’s exact test and the significance level of the test was targeted at 0.05. Assuming a 10 % drop-out rate, approximately 62 patients (total) will need to be recruited.

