#### Primary outcome

The primary analytical approach will be to evaluate all randomized patients in an intention to treat analysis. Differences in the primary outcome measure, proportion with 25OHD <50 nmol/L, between the treatment groups will be evaluated using the Fisher’s exact test. Logistic regression analysis will be used if important variables are unevenly distributed between groups. We anticipate minimal missing data because more than 95 % of participants from the recently completed observational study had an immediate postoperative sample [26].

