### Safety measures and clinically relevant research findings

A flow diagram depicts the safety measures in place and response to clinically relevant research findings for individual study participants (Additional file 3). A standard operating procedure has been developed for adherence to the following safety measures.

To avoid vitamin D overdose, hypercalcemia and side effects, we have selected a supplement level recently proven to be safe in healthy children and will target the period of high-dose supplementation to 6 months and no more than 12 months. Study participants with elevated blood calcium and/or vitamin D levels will be identified and contacted by the safety officer. For 25OHD, although 500 nmol/L is generally considered the definitive acute toxicity threshold, we have chosen to intervene with 25OHD levels above 200 nmol/L as this value is supraphysiological and exceeds our study goal. The following details the actions that will be taken with abnormal values:For 25OHD above 200 nmol/L with evidence of hypercalcemia (vitamin D toxicity), discontinue study drug immediately, repeat the values (fasting), and refer to endocrinology.For 25OHD above 200 nmol/L without hypercalcemia, the study drug will be reduced by 50 %; (c) For 25OHD above 250 nmol/L, without hypercalcemia: study drug will be discontinued.For hypercalcemia with 25OHD under 200 nmol/L, repeat the bloodwork (fasting) and refer to endocrinology.

Both postoperative hypo- and hypercalcemia will be managed by the clinical team as required. Study participants with persistently elevated blood calcium levels (for more than 2 days, not explained by intravenous calcium administration) will be referred to endocrinology (Additional file 3).

As prolonged exposure to hypercalciuria (>3 months) could theoretically cause nephrocalcinosis, we will have ultrasounds performed prior to hospital discharge on all patients with elevated immediate preoperative urine calcium to creatinine ratios. Any study participant with nephrocalcinosis will be referred to the nephrology service for further assessment.

Participants that have study drug discontinued or decreased will be retained in the study, have perioperative biological samples collected as outlined, and will be included in the analysis using intention to treat methodology.

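### An unqualified sentence limiting analyses to children who complete the whole protocol contradicts the intention-to-treat rule stated elsewhere and needs to be deleted or confined to a supportive analysis

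*Protocol article*

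**What the plan says.** Three places in the protocol article say who is analysed.

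- **Primary outcome:** "The primary analytical approach will be to evaluate all randomized patients in an intention to treat analysis".
- **Safety measures and clinically relevant research findings:** "Participants that have study drug discontinued or decreased will be retained in the study"; these children have their perioperative samples taken and "will be included in the analysis using intention to treat methodology".
- **Subgroup analysis, last sentence of the Feasibility paragraph:** "Only those children completing the entire study protocol will be included in analyses".

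Two further passages bear on what completion could mean. Under Prior to initiation of study drug, initiation samples are requested but "children will still be enrolled if these samples cannot be collected or the families do not want these procedures"; the Figure 1 caption says the same. Under Primary outcome, loss of the endpoint is expected to be small: "We anticipate minimal missing data because more than 95 % of participants from the recently completed observational study had an immediate postoperative sample".

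**The concern.** A randomized child who does not complete the protocol is in the analysis under the first two rules and out of it under the third. The article does not say which rule prevails, and it does not define completion.

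The primary endpoint needs one blood sample on the day of ICU admission. The protocol schedules much more: initiation samples, operating-room samples, postoperative blood on days 1, 3, 5 and 10 or at discharge, urine and echocardiography. Read literally, the completers sentence could exclude a child who has the primary endpoint because an unrelated sample is missing.

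Such exclusions happen after allocation and need not be balanced:

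- Dose reductions and stops are triggered by 25OHD above 200 or 250 nmol/L. The article cites mean levels of 130 to 150 nmol/L at doses near the high dose, so these events would be expected mainly in that arm, and in children who are not deficient.
- The Subgroup analysis section expects serious lesions in neonates to limit delivery of enteral drug. Those children are more likely to be deficient.

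Removing the first group understates the high dose, and removing the second flatters it. What is at stake is whether the comparison still rests on randomization, in a trial of 62 children.

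**Working it through.** **1. The plan's own sample size.** Inputs from Sample size justification: 40% v 80% above 50 nmol/L, two-sided Fisher's exact test ("The test statistic used is the two-sided" Fisher's test), alpha 0.05 ("significance level of the test was targeted at 0.05"), 80% power, 28 per arm, 10% drop-out, 62 in total.

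- Exact power is the sum, over all pairs (x, y) with Fisher p ≤ 0.05, of Bin(x; n, 0.40) × Bin(y; n, 0.80). It is 80.2% at n=27 and 82.3% at n=28. The normal formula with continuity correction gives 28 per arm.
- 56 × 1.10 = 61.6, so 62; 56 / 0.90 = 62.2, so 63.

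The stated figures reproduce. The sample size is not in question, and the drop-out allowance concerns recruitment, not who is analysed.

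**2. The rules side by side.**

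| Randomized child | Primary outcome section | Safety section | Completers sentence |
|---|---|---|---|
| Drug stopped or reduced, postoperative sample taken | in | in | out, if completion includes dosing |
| Took drug, has the ICU-admission sample, initiation or later sample missing | in | not addressed | out, if completion includes all samples |
| No postoperative sample | in | not addressed | out |

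The rows conflict unless completion means no more than reaching surgery and giving the postoperative sample. Even then the third row conflicts.

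**3. Effect near the significance boundary (assumed counts above 50 nmol/L, 31 per arm, two-sided Fisher).**

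- All randomized: 20/31 (64.5%) v 12/31 (38.7%), p=0.074.
- Drop 4 deficient high-dose and 2 deficient usual-care children: 20/27 (74.1%) v 12/29 (41.4%), p=0.017. The number dropped, 4 + 2 = 6, equals the drop-out allowance, 62 − 56 = 6.
- Opposite direction: 21/31 (67.7%) v 12/31, p=0.041. Drop 3 non-deficient high-dose children whose drug was stopped: 18/28 (64.3%) v 12/31, p=0.069. This case arises only if the completers sentence overrides the safety section, which includes these children.

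**4. Effect at about the planned rates.**

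- All randomized: 25/31 (80.6%) v 12/31 (38.7%), p=0.0016.
- Drop 3 non-deficient high-dose children: 22/28 (78.6%) v 12/31, p=0.0034. The conclusion is unchanged.

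**5. False-positive rate under a one-sided loss (assumed).** Suppose both arms have the same true proportion p above 50 nmol/L, and a fraction d of the high-dose arm, with proportion q above 50, is dropped. The high-dose completers then show (p − dq)/(1 − d).

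- p=0.60, d=0.10, q=0.20: (0.60 − 0.02)/0.90 = 0.644. Fisher rejection with 28 v 31 children is 4.2%.
- p=0.60, d=0.25, q=0: 0.60/0.75 = 0.80. Rejection with 23 v 31 is 28.7%.
- All 31 per arm analysed: 2.8%.
- With p=0.40 and the same range of d and q, rejection runs from 4.0% to 11.4%, against 2.8%.

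These figures put all the loss in one arm. Few and balanced exclusions would have a small effect.

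**The case against.** The best defence is the position of the sentence. It closes a Feasibility paragraph about neonates and other short-exposure infants, and two more specific statements elsewhere commit to intention to treat, one of them for the very children whose drug is stopped or reduced. A reader might infer that the sentence turns the whole trial into a completers comparison. The documents do not support that: the section governing the primary outcome says the opposite, and the text reads as one stray sentence against two deliberate ones.

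Other parts of the defence have weight:

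- Completion is undefined. If it means reaching surgery and giving the postoperative sample, the conflict shrinks mainly to children without an outcome, expected to be fewer than 5%.
- Children with disease preventing enteral feeds or drug before surgery are already ineligible, which narrows the group lost for that reason.
- No rate is given for levels above the 200 nmol/L trigger, so arm-dependent stopping is plausible but not quantified.
- The counts that cross p=0.05 were chosen close to it.

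What the defence does not remove is the wording, which has no limit to the subgroup. Nor does the narrow reading rescue it. The subgroup's aim is the proportion deficient in each arm, with 12 children considered enough to exclude 75%. A completers rule would remove the children in whom failure to deliver the drug is part of the answer.

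**Conclusion.** The contradiction is real and the sentence is wrong as written. If followed, for the primary comparison or for the subgroup alone, it would exclude randomized children on grounds that can depend on arm and prognosis, in either direction.

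The size of any bias cannot be derived from the article, because neither the number nor the type of non-completers is known. Three to six exclusions can change significance when the result lies near 0.05. At about the planned 80% v 40%, losing three high-dose successes does not. The false-positive figures of 4.2% to 28.7% rest on an assumed loss of 10% to 25% from one arm only, at a common true rate of 60%, and are not a forecast.

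**What to change.** Delete the last sentence of the Subgroup analysis section and state instead:

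- Primary, secondary and subgroup comparisons follow intention to treat in all randomized children, in the arm assigned, regardless of dosing received or completion of other samples. This agrees with the Primary outcome and safety sections.
- Children without the postoperative 25OHD sample are reported by arm with reasons, and covered by a simple sensitivity analysis, for example counting them as deficient and then as not deficient. Limiting the analysis to children with a sample, without saying this, would replace one restriction with another.
- Any completers analysis is a labelled supportive per-protocol analysis, with completion defined before unblinding.

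The cost is a few lines of text. No patients or measurements are added and the target of 62 stands. For orientation, exact power at 40% v 80% is 87.0% with all 31 per arm observed. It is 76.9% if an assumed 10% per arm have no sample and are counted as deficient (0.40 × 0.90 = 36% v 0.80 × 0.90 = 72%). The loss would be smaller at the missing rate of under 5% that the article expects. With 62% of the target enrolled at the time of writing, the change can be made before the analysis.
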